#### Secondary outcome

A. The most important secondary outcome is the Michigan Neuropathy Screening Instrument (MNSI) [41] scores at week 4 (the end of treatment). We will assess MNSI at baseline, week 2, week 8  and week 12. MNSI is comprised of the history questionnaire and the physical assessment. The history questionnaire is self-administered by the patients. Responses of “yes” to items 1–3, 5–6, 8–9, 11–12, and 14–15 are each counted as one point. A “no” response on items 7 and 13 counts as 1 point. Item 4 is a measure of impaired circulation, and item 10 is a measure of general asthenia and is not included in scoring [41]. The physical assessment comprises appearance of feet, ulceration, ankle reflexes, vibration perception at great toe, and monofilament and will be completed by a health professional.

B. Diabetes-Specific Quality of Life (DSQL) [42] will be used to assess health-related quality of life at baseline, week 4, week 8 and week 12. It mainly reflects the influence of diabetes and its treatment on the physiological, psychological, and social relations of patients. It has four dimensions: physiological function, psychological spirit, social relations, and the influence of treatment. DSQL has a total score of 120. The lower the score, the less affected by the disease and the better the quality of life.

C. Blood rheology parameters including whole blood low shear reduction viscosity, high shear reduction viscosity, plasma viscosity, and erythrocyte aggregation index will be measured at baseline and week 4.

D. Assessment of safety

We will collect any adverse event, whether related to treatment or not by the patients and practitioners at every session. During the 4-week follow-up period (from week 5 to week 12), we will telephone each patient every week to record any adverse event or side effect that occurs. Possible side effects of 10.6-μm laser moxibustion include redness and blisters. Serious adverse effects are reported to Medical Ethics Committee. The patients will answer questionnaire assessing the safety of the treatment at the end of LM treatment (week 4): “What do you think of the safety of laser therapy: safe, relatively safe, unsafe, and very unsafe” [39].

E. Blinding assessment

The patients in both groups will be asked to guess their group assignment allocation after the first treatment session and the end of treatment as following: “which group do you think you are in: A. 10.6-μm laser moxibustion; B. non-10.6-μm laser moxibustion; or C. not sure.” And the operators operating the true or sham LM devices will be also asked to answer the similar question.

J. Usage of medication

Medication usage log: The participants will be asked to record medications especially when changing the type or dosage compared with listed in Table 2.

The summarization of data collection plan is showed in Table 3.

**Table 3 Tab3:** The summarization of data collection

	Baseline	Week 2	Week 4	Week 8 and Week 12(follow-up)
Demographic characteristics^a^	√	—	—	—
FPG,2hPBG, HbA1c	√	√	√	√
NCV	√	—	√	—
MNSI	√	√	√	√
DSQL	√	—	√	√
Blood rheology parameters	√	—	√	—
Assessment of safety	—	√	√	√
Blinding assessment	—	—	√	—
Intake of medicine	√	√	√	√

^a^ Demographic characteristics include age, sex, course of DM, course of DPN, BMI, and level of education

### Data management

The data will be double entered by two researchers who do not participate in other processes respectively.

We plan to hold mid-term report meetings twice a year to monitor patient safety and treatment efficacy data while the trial is ongoing.

### Statistical analysis

The statistical analysis will be performed using SPSS version 21.0 software. All continuous data that follow the normal distribution will be expressed as mean ± standard deviation (); data that do not conform to the normal distribution will be expressed as median (Q1, Q3). And categorical data will be expressed in terms of the number of cases. If the general numerical data follow normal distribution, then the independent sample *t* test will be used to analyze the differences between the two groups at different points in time. If the values do not follow normal distribution, then the Wilcoxon Mann-Whiney *U* rank sum test will be used. Chi-square test and Mann-Whitney *U* test will be used to analyze the categorical data. Differences are considered statistically significant at a *P* value less than 0.05.

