### Sample size

According to the studies [36, 37], we assume that the peroneal motor nerve conduction (MNCV) velocity in the LM group increases by 38% after treatment and that in the sham LM group by 16% after treatment. Fifty-one patients per group will be required with an alpha of 0.05 and a power of 0.8. Considering possible drop-out (i.e., 10% drop-out) during the trial, we will recruit 57 patients for each group.

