### Outcome measures

#### Primary outcome

##### Nerve conduction velocity (NCV)

NCV will be performed on both lower extremities at baseline and the week 4 (the end of treatment). Peroneal motor nerve conduction velocity (MNCV), sural sensory nerve conduction velocity (SNCV), and tibial motor nerve conduction velocity (MNCV) will be measured.

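### The planned t or Mann-Whitney comparison leaves out the baseline values that are collected; it is valid, but less efficient than ANCOVA and, read literally, does not test the increase the trial was sized on

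*Protocol article*

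**What the plan says.** The Statistical analysis section of the protocol article names the between-group test for continuous outcomes. For normal data an independent-sample t test "will be used to analyze the differences between the two groups at different points in time". Otherwise: "If the values do not follow normal distribution, then the Wilcoxon Mann-Whiney *U* rank sum test will be used". No change score, baseline covariate or regression model is named, and the choice between the two tests depends on the observed distribution.

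The Sample size section works from an increase. It assumes that peroneal motor nerve conduction "velocity in the LM group increases by 38% after treatment and that in the sham LM group by 16% after treatment". It then states: "Fifty-one patients per group will be required with an alpha of 0.05 and a power of 0.8". With 10% drop-out this becomes 57 per group. No SD is given, for the velocity or for its increase, and no correlation between baseline and week 4.

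The baseline values exist. Under Primary outcome: "NCV will be performed on both lower extremities at baseline and the week 4 (the end of treatment". Table 3 also schedules MNSI at baseline and weeks 2, 4, 8 and 12, and DSQL at baseline and weeks 4, 8 and 12.

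**The concern.** When an outcome is measured before and after treatment, the baseline value usually explains part of the spread in the later value. A test that ignores it leaves that spread in the error term. ANCOVA removes it and estimates the same treatment difference with a smaller standard error.

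There is also a mismatch inside the protocol. The sample size concerns an increase from baseline, whereas the analysis section, taken at its word, compares the groups at a time point. For NCV the only time point after baseline is week 4, so this is one comparison per nerve measure. The two quantities have different variances, so power planned on one does not carry over to the other.

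Finally, the test is not fixed in advance. Three nerve measures make up the primary outcome, and the normality check could lead to a comparison of means for one and a rank test for another. At stake are the precision of the primary result and a single effect measure settled before the data are seen.

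**Working it through.** **The plan's own figures.** Drop-out: 51 / (1 − 0.10) = 56.7, so 57 per group, which agrees with the protocol. The 51 itself cannot be rebuilt as a comparison of mean increases, because no SD is given. Solving backwards (two-sided 0.05, 80% power, normal approximation), the standardized difference is (1.960 + 0.842) × √(2/51) = 0.555. With a difference of 38 − 16 = 22 percentage points, the implied SD is 22 / 0.555 ≈ 39.7 points. This shows what 51 would need; it does not confirm how 51 was obtained.

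**Variances.** Take equal SDs at baseline and week 4 and correlation rho (assumed). Relative to the variance of the week-4 value:

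- week-4 value alone: 1
- change from baseline: 2(1 − rho)
- ANCOVA residual: 1 − rho²

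Power at 51 per group is Φ(2.802 / f − 1.960). Here 2.802 = 1.960 + 0.842, and f is the SD of the method used divided by the SD on which the 80% was planned.

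**Case A: 51 per group gives 80% power on week-4 values.** For ANCOVA f = √(1 − rho²), and the number per group for 80% power is 51 × (1 − rho²), rounded up.

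| rho (assumed) | Week-4 test | ANCOVA | n per group, ANCOVA at 80% |
|---|---|---|---|
| 0.3 | 80% | 83.6% | 47 |
| 0.5 | 80% | 89.9% | 39 |
| 0.7 | 80% | 97.5% | 27 |

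Example, rho 0.5: f = √0.75 = 0.866; 2.802 / 0.866 − 1.960 = 1.275; Φ(1.275) = 89.9%.

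**Case B: 51 per group gives 80% power on the change.** For the week-4 test f = 1 / √(2(1 − rho)). For ANCOVA f = √((1 − rho²) / (2(1 − rho))) = √((1 + rho) / 2).

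| rho (assumed) | Week-4 test | ANCOVA |
|---|---|---|
| 0.3 | 91.2% | 93.5% |
| 0.5 | 80.0% | 89.9% |
| 0.6 | 70.7% | 87.9% |
| 0.7 | 58.3% | 86.0% |
| 0.8 | 42.5% | 84.0% |

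Example, rho 0.7: week-4 test, 2.802 × √0.6 − 1.960 = 0.210, Φ = 58.3%; ANCOVA, 2.802 / √0.85 − 1.960 = 1.079, Φ = 86.0%.

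In Case B the week-4 test falls below the planned 80% only when 2(1 − rho) < 1, that is, when rho > 0.5. In both cases ANCOVA is ahead at every rho shown.

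**The normality switch.** A simulation with 51 per group and 20,000 runs chose between the t test and the Mann-Whitney test by Shapiro-Wilk. Type I error was 0.050 for normal data and 0.049 for lognormal data. Power for normal data was 79.2%, against 79.4% for the t test alone.

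**The case against.** **The analysed variable is not spelled out.** The protocol never says that the raw week-4 level is tested. The same t test could be run on the increase, and the Sample size section points that way. This stands in part: the mismatch follows from a literal reading and is not certain. But the section does not name the increase, and if change scores were meant, ANCOVA would still be at least as efficient apart from one degree of freedom.

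**The size is unknown.** This stands. The documents give neither SD nor rho, and Case B assumes that 51 came from a two-sided comparison of mean changes. The protocol also speaks of percentage increases, while the factor 2(1 − rho) belongs to absolute change. Taken literally, an SD of change of 39.7% of baseline would imply a between-patient SD of 39.7 / √0.8 ≈ 44% of baseline at rho 0.6 and 39.7 / √0.4 ≈ 63% at rho 0.8. The steep losses at high rho are therefore illustrations. That NCV varies more between patients than within them over four weeks would favour a high rho, but the protocol does not say so.

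**Three stronger readings do not hold.** A reader might infer that chance baseline imbalance biases the result; under randomization the unadjusted test is valid and its standard error already allows for such imbalance. A reader might infer that the normality switch inflates false positives; the simulation shows practically no cost, and the fault is only that the primary test is not fixed in advance. A reader might infer that separate tests per visit discard patients; each test uses everyone seen at that visit, the withdrawal section promises an intention analysis of all cases, and missing-data methods may stand in an analysis plan not shown.

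**This belongs in the analysis plan.** It would if the article were silent, but the article states the test, and the point concerns that stated choice.

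**Conclusion.** The point holds as a matter of efficiency and of agreement with the sizing. The stated test ignores baseline values that the trial collects, and ANCOVA is more powerful for any appreciable rho. On a literal reading, the test also addresses a different quantity from the one behind the 51 per group.

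Only the direction of the loss relative to ANCOVA is certain. Its size depends on an assumed rho, equal SDs and an assumed basis for the 51. At rho 0.5, ANCOVA gives about 90% power where the week-4 test gives 80%, in both cases examined. A reader might conclude that the trial will miss its planned 80% power; the documents do not support that, since against change-based sizing the week-4 test falls short only above rho 0.5 and has 91% at rho 0.3. Because the correction costs almost nothing, it should be made.

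**What to change.** In the Statistical analysis section, and in the analysis plan if there is one:

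- Make the primary NCV analysis an ANCOVA of the week-4 value on group, with the baseline value of the same measure as covariate. Fix it in advance, whatever the normality check shows.
- Report the adjusted group difference with its 95% CI. Keep a rank-based analysis as sensitivity only.
- Apply the same baseline adjustment to MNSI and DSQL, for example in a mixed model across visits with group, visit, group-by-visit and baseline, and with week 4 as the key MNSI contrast.
- State the SD and the baseline to week-4 correlation assumed for the sample size, and whether it rests on the change or on the week-4 value.

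The first three are wording changes, done before unblinding, with standard procedures in the software already named (UNIANOVA and MIXED in SPSS). The fourth means writing down the assumptions behind the existing figure. No new data, visits or patients are needed.

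### Separate per-visit tests of MNSI and DSQL ignore baseline and earlier scores and, unless missing values are imputed, do not fit the promised all-cases analysis

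*Protocol article*

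**What the plan says.** All references are to the protocol article.

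- **Statistical analysis.** For normally distributed data, an independent-sample t test "will be used to analyze the differences between the two groups at different points in time". The fallback is also cross-sectional: "If the values do not follow normal distribution, then the Wilcoxon Mann-Whiney" test is used. No longitudinal model and no baseline covariate is named.
- **Secondary outcome, A.** MNSI at the end of treatment (week 4) is ranked first among the secondary outcomes, and the text adds "We will assess MNSI at baseline, week 2" and weeks 8 and 12. With week 4, which Table 3 confirms, that makes five visits, four of them after baseline.
- **Secondary outcome, B.** DSQL "will be used to assess health-related quality of life at baseline, week 4, week 8 and week 12": four visits, three of them after baseline.
- **Principles of management of withdrawal.** Patients who withdraw are to have whatever assessments are still feasible, and all cases enter an intention analysis.
- **Sample size.** "Considering possible drop-out (i.e., 10% drop-out) during the trial", 51 per group becomes 57 per group.

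The article does not say how a missing score enters a test.

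**The concern.** MNSI and DSQL are repeated measures on the same patients, but the stated method treats each visit as a fresh two-sample comparison. Two things follow.

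First, the baseline score, usually a strong predictor of a later score on the same scale, is not used, so the comparisons are less precise than the scheduled data allow.

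Second, a two-sample test needs a value from each patient at the visit tested. If nothing is imputed, a patient who leaves after week 4 contributes nothing at weeks 8 and 12, although three MNSI scores are on file. The promise to analyse all cases and the named tests then pull apart. If those who leave differ in outcome from those who stay, and do so differently by arm, the comparison is biased. At stake are MNSI at week 4, which the article ranks first among the secondary outcomes, and weeks 8 and 12, which supply the only follow-up efficacy data.

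**Working it through.** **1. The plan's drop-out figure.** 51 / (1 − 0.10) = 56.7, rounded up to 57, as stated. Conversely 57 × 0.90 = 51.3, so about 51 patients per arm would have a final score and about 6 would not.

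**2. What a per-visit test uses.** Without imputation, a patient with MNSI at baseline, week 2 and week 4 who then leaves for good is absent at weeks 8 and 12. A patient who misses only week 8 is absent only at week 8. A patient with a week-2 score but no week-4 score is absent from the key MNSI comparison. For DSQL no visit lies between baseline and week 4, so at week 4 only the baseline score goes unused.

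**3. Precision from the baseline score.** With correlation ρ between baseline and the later score, adjustment multiplies the standard error by about √(1 − ρ²). The article gives no ρ; 0.5 to 0.7 is assumed.

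- ρ = 0.5: √0.75 = 0.866, a 13% cut.
- ρ = 0.7: √0.51 = 0.714, a 29% cut.
- With an assumed MNSI SD of 2.5 and 51 per arm, the unadjusted standard error is 2.5 × √(2/51) = 0.495. It falls to 0.429 or 0.353.
- If the tests were run on change from baseline, which the text does not say, the factor would be √((1 + ρ)/2). That is 0.866 or 0.922, a cut of 13% or 8%.

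**4. Bias when there is a true effect.** Monte Carlo, 1500 runs per setting, every input assumed except 57 per arm: SD 2.5, true week-12 MNSI difference 1.0, visit correlation constant or decaying, drop-out driven by the last observed score.

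- Loss of 15% under sham and 4% under LM (average 9.5%, close to the planned 10%): the per-visit difference averages 0.76 to 0.90 across settings, 10% to 24% too small. Baseline-adjusted analysis of those with a value gives 0.88 to 0.96. A likelihood model using all visits gives 0.99 to 1.02.
- Loss of 10% and 9%: the per-visit bias is at most about 4%.

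The largest bias, 0.24, is 0.24 / 0.495 = 0.48 of a standard error; 0.04 is 0.08 of one. No week-4 simulation was run.

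**5. Bias when there is no effect.** 57 per arm, correlation 0.5 to 0.7, nominal 10% or 20% loss by week 12 depending on the previous score, 800 runs.

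- Same drop-out mechanism in both arms: per-visit bias −0.02 to 0.00 SD, type I error 5.0% to 6.5% (simulation standard error √(0.05 × 0.95 / 800) = 0.8 percentage points).
- Opposite mechanisms in the two arms, a worst case: bias 0.15 to 0.36 SD and type I error 11% to 40%. At nominal 10% loss alone the figures are 0.15 to 0.21 SD and 11% to 17%.
- Likelihood model using all visits: bias within 0.02 SD in both cases.
- Standard errors at 10% loss: 0.196 to 0.206 for the per-visit test against 0.188 to 0.205 for the model. That model fitted a free mean for each arm at every visit, baseline included, so this small gain comes from borrowing across visits and excludes the gain in step 3.

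**The case against.** A reader might infer more than the article supports.

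- **That only attenders are analysed and others are discarded.** The article does not say so. It names a test, not a rule for missing values, and that rule is commonly left to an analysis plan or full protocol, neither of which is shown. Silence on imputation is therefore no finding. The withdrawal section, if anything, points toward keeping patients in.
- **That per-visit testing cannot deliver an all-cases analysis.** It can: t tests on imputed data may include every randomised patient and draw on intermediate visits.
- **That follow-up effects will be understated by a fifth or so.** This needs an assumed split such as 15% against 4%. The Sample size section gives 10% with no difference between arms, and the sham device is built to look and operate like the active one. With similar loss the bias is trivial, and its direction depends on who leaves.
- **That the trial's main result is at risk.** Nerve conduction velocity is measured only at baseline and week 4, so this point does not touch it.

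It is also fair that a mixed model does not include all cases either, since patients with no post-baseline score remain outside it.

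All of this stands. It does not remove the criticism of the method that the article does commit to: two-sample tests at each time point that use neither the baseline nor earlier scores.

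**Conclusion.** The concern holds in a limited form. For MNSI and DSQL the article fixes separate cross-sectional tests. These forgo information already scheduled for collection and, unless missing values are imputed, do not match the intention analysis of all cases. The more certain loss is precision: about 13% to 29% of the standard error, resting on an assumed baseline correlation of 0.5 to 0.7 and on the tests being applied to the scores themselves. Bias is a conditional risk that requires loss that is both outcome-related and different between arms; the article does not show that this will occur. The point concerns secondary outcomes only. The change is worth making before the data are analysed, because it is cheap and protects the secondary outcome that the article ranks first.

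**What to change.** For MNSI and DSQL, make one mixed model for repeated measures per outcome the main analysis:

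- fixed effects for arm, visit, arm-by-visit and baseline score; unstructured covariance; REML;
- every randomised patient with at least one post-baseline value included;
- the week-4 MNSI contrast with its 95% confidence interval as the key secondary result, with weeks 8 and 12 read from the same model;
- the per-visit rank test kept as a sensitivity analysis;
- the number of patients with no post-baseline score reported by arm (for DSQL, anyone leaving before week 4), and the all-cases statement in the withdrawal section reworded to match.

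The cost is analysis wording only; no visit, measurement or patient is added. The model assumes data missing at random given the observed scores and roughly normal residuals. The first assumption is weaker than what unimputed per-visit tests need; the rank test gives a check on the second.

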## Discussion

DM is another major killer of human health in addition to malignant tumors and cardiovascular diseases. DPN, a common complication of DM, is the main cause of disability in DM patients and seriously affect the quality of life of patients. Drugs for improving microcirculation, correcting metabolic disorders and nourishing the nerves as well as for pain management are used to treat DPN. Because of their limited effectiveness on symptomatic relief and undesirable side effects, to find a convenient and effective therapy which can not only improve the symptom of DPN but also reduce the dosage of drugs and avoid the serious side effects is necessary. The 10.6-μm LM used in our research produces a thermal effect similar to that of traditional moxibustion but without smoke and smell. Besides, compared with the traditional moxibustion, the 10.6-μm LM is much easier and safer to operate and control with adjustable parameters. We can know the quantitative data of the therapy dosage that we can’t get if we use the traditional moxibustion therapy.

This is a double-blind, sham-controlled trial. The sham LM device is identical with the LM device in appearance, and operational procedure. To achieve successful masking, the two groups of patients are treated in separate rooms or treatment time, and the active or sham devices are operated by different trained operators. The participants and the devices operators are not informed explicitly that either true or sham laser treatment will be given. They are only informed that either 10.6-μm laser moxibustion or non-10.6-μm laser moxibustion will be given. The study design is a rigorous double-blind RCT, the arrangement of the trial process and the characteristics of the true and sham laser device make the blind method more reasonable.

The selected acupoints, ST36 (Zú Sān Lǐ), GB34 (Yáng Líng Quán), SP6 (Sān Yīn Jiāo), and KI3 (Tài Xī), are commonly used points for DPN [43]. These acupoints are located on the lower limbs and can help to replenish qi and the blood, warm the meridians, and improve blood circulation and disperse stasis through moxibustion.

In our study, we will use the nerve conduction study (NCS) as the primary outcome. NCS is also one of the objective measures in the diagnosis of DPN with high sensitivity and accuracy [44]. Besides, we will use the symptoms and examination outcome measurement (MNSI) to evaluate the severity of the symptom. The subjective outcome (DSQL) will be used to assess the influence of the treatment on patients’ quality of life. The blood rheology parameters will be used to assess the effect of 10.6-μm LM on improving blood rheology and decreasing blood viscosity in DPN patients.

There are two limitations of our study. Firstly, we focus more on the clinical effect of LLLT on DPN, not much attention has been paid to the possible mechanism of LLLT on DPN. Secondly, due to the limitations of the device, one treatment will last for 30 min, but each acupoint will be irradiated for 15 min.

A study showed that the increasing of NCV in the mecobalamin combined moxibustion group was higher than that in the mecobalamin alone group at the same endpoints [36]. Thus, we anticipate the 10.6-μm LM which shared similar infrared effect with the traditional moxibustion may result in similar curative effect and reduce the dosage of drugs as well as avoiding the serious side effects caused by western medicine. We expect this double-blind, sham-controlled trial will provide rigorous evidence for the effect and safety of 10.6-μm LM as adjuvant therapy in treating DPN.

